# Does the I-CARE e-learning programme improve primary care physicians’ competence in LGBTI health? Protocol for a two-arm, parallel-group, superiority randomised controlled trial in French-speaking Switzerland (EFFICARE study)

**DOI:** 10.1136/bmjopen-2026-119896

**Published:** 2026-08-04

**Keywords:** Health Equity, Vulnerable Populations, MEDICAL EDUCATION & TRAINING, Primary Care, Sexual and Gender Minorities, Randomized Controlled Trial

## Abstract

**Introduction:**

Lesbian, gay, bisexual, transgender or non-binary and intersex (LGBTI) populations experience persistent health inequities, including poorer mental and physical health outcomes and higher unmet healthcare needs compared with non-LGBTI populations. These inequities are partly attributable to insufficient training of primary care physicians (PCPs) in LGBTI health. However, evidence on effective and scalable training interventions for PCPs remains limited, particularly outside North America. This study evaluates the effectiveness of a self-directed e-learning programme—Improving Care and Access for Rainbow Equity (I-CARE)—designed to improve PCPs’ knowledge, attitudes, skills and behaviours related to LGBTI health.

**Methods and analysis:**

We will conduct a type I effectiveness-implementation hybrid, two-arm, parallel-group, superiority randomised controlled trial among PCPs practising in French-speaking Switzerland. Eligible physicians will be randomly assigned (1:1) to either the I-CARE programme (intervention) or an e-learning programme on motivational interviewing (control) matched for format and duration. Outcomes will be measured at baseline, immediately postintervention and at the 3-month follow-up. The primary outcomes are knowledge and attitudes towards LGBTI patients assessed at the postintervention time point using validated scales. Superiority will be declared if the intervention group is statistically significantly superior to the control group on at least one primary outcome and statistically significantly inferior on neither primary outcome. Secondary outcomes include skills, self-reported behaviours and the presence of LGBTI-inclusive environmental cues. Effectiveness will be analysed using generalised estimating equations. Implementation outcomes will be evaluated using the Reach, Effectiveness, Adoption, Implementation and Maintenance (RE-AIM) framework.

**Ethics and dissemination:**

Participants will provide electronic informed consent. All study data will be managed and stored on secure servers hosted by the Lausanne University Hospital (CHUV). All information will be handled in strict accordance with the Swiss Federal Act on Data Protection. The project was approved by the Central Ethics Commission of the University of Lausanne on 7 July 2025 (C_Services centraux_052025_00018). Study findings will be disseminated through peer-reviewed scientific publications and lay summaries intended for the public, Swiss PCPs and LGBTI communities.

**Trial registration number:**

ISRCTN93781961 (11 March 2026, updated 14 July 2026)

STRENGTHS AND LIMITATIONS OF THIS STUDYThe randomised design with an active control programme matched for format, duration and continuing medical education credits allows any between-group difference to be attributed to content addressing the health of lesbian, gay, bisexual, transgender or non-binary and intersex (LGBTI) people rather than to attention or incentive effects.Stratified block randomisation protects against chance imbalance between arms on sex and age, two factors associated with physicians’ attitudes towards LGBTI patients.The use of validated, culturally adapted instruments and a 3-month follow-up enables reliable assessment of both immediate and sustained training effects.Reliance on self-reported outcomes may introduce social desirability bias, which partial blinding to the study hypothesis can only partly mitigate.Voluntary participation may limit the representativeness of the sample relative to all eligible primary care physicians.

## Introduction

 Lesbian, gay, bisexual, transgender or non-binary and intersex (LGBTI) individuals experience substantial health inequities compared with non-LGBTI individuals, including higher prevalence of mental health conditions, substance use, certain chronic diseases and barriers to healthcare access.^1–6^ Minority stress theory posits that structural, interpersonal and internalised stigma generate chronic stress, thereby contributing to adverse health outcomes.^7
8^ In Switzerland, 27% of LGBT people have experienced discrimination and violence in the healthcare setting because of their sexual orientation and/or gender identity,^6^ a pattern also observed in other countries.^9^ The proportion of LGBT people who forgo care due to a lack of trust in the healthcare system is more than two times that of the Swiss population (16.2% vs 6.9%).^6^ Implicit bias and lack of training among healthcare professionals (HCPs) have been hypothesised as important individual-level barriers contributing to the unmet health needs of LGBTI individuals.^10^

Although some HCP training programmes on LGBTQ+ health have been developed, evidence on their effectiveness is limited.^11^ A systematic review on educational interventions to reduce LGBTQ-related bias among medical, nursing and dental students and providers showed that bias-focused training programmes were associated with increased knowledge on LGBTQ healthcare issues.^12^ Another systematic review reported short-term improvements in knowledge and attitudes among healthcare students and professionals regarding LGBT-specific healthcare.^13^ A recent systematic review found that among 44 studies, improvement was shown among health professionals for knowledge (28 studies), attitudes (14 studies) and behaviours (seven studies).^11^ These studies, however, face important limitations. First, more than half of the studies had a sample size smaller than 100 and more than 80% of these studies were conducted in the USA, with only one being conducted in Europe. Second, most of the studies in these reviews did not involve a control group or used a randomised controlled experimental design, making it difficult to attribute changes to exposure to the programme. Third, many of these studies neither distinguished primary care physicians (PCPs) from other HCPs nor considered implementation outcomes (eg, adoption, acceptability).^14^

E-learning approaches offer scalable and cost-effective opportunities for continuing medical education (CME). A meta-analysis of studies on internet-based learning among health professions found that online training (on a wide range of medical topics) is as effective as traditional methods for improving knowledge, attitudes, skills and behaviours.^15^ A separate review of e-learning facilitators^16^ identified factors that predict effectiveness, including how user-friendly technologies were, flexibility of use, adaptation to the pace of learners, transferability of knowledge to clinical practice and the use of clinical case studies. On the other hand, lack of information technology (IT) skills was identified as a potential barrier to the use of e-learning methods by physicians.^17^

Using a randomised controlled trial design, we aim to evaluate the effectiveness of the Improving Care and Access for Rainbow Equity (I-CARE) programme in improving PCPs’ knowledge, attitudes, skills, self-reported behaviours and use of inclusive environmental cues related to LGBTI health. We hypothesise that, compared with an active control group receiving an e-learning programme on motivational interviewing (MI), I-CARE will lead to greater improvements in these outcomes. Additional implementation outcomes—reach, adoption, implementation fidelity and maintenance—will be assessed using the Reach, Effectiveness, Adoption, Implementation and Maintenance (RE-AIM) framework.

## Methods and analysis

### Study design and setting

This study is a type I effectiveness–implementation hybrid, two-arm, parallel-group, superiority randomised controlled trial with a 1:1 allocation ratio. It is conducted among PCPs practising in the French-speaking cantons of Switzerland (Fribourg, Geneva, Jura, Neuchâtel, Valais, Vaud and Bern), which comprise about one quarter of the Swiss population. Participants are individually randomised to receive either the I-CARE e-learning programme (intervention) or an active control e-learning programme on MI, matched for format and duration. Outcomes are assessed at baseline, immediately postintervention, and at the 3-month follow-up assessment. Participants are partially blinded to the specific study hypothesis but not to group allocation. The trial incorporates implementation outcomes evaluated using the RE-AIM framework.

### Participants

All PCPs holding eligible specialist titles and practising in the study region, as identified through a specialised private registry (estimated N=5601), will receive a postal invitation containing the study website address. Additional communication strategies may include announcements through cantonal medical societies, professional networks and conferences.

### Inclusion criteria

Eligible participants include PCPs practising at least 1-day per week in the study region, holding a recognised Swiss specialist title in general internal medicine, paediatrics, gynaecology, psychiatry or the ‘médecin praticien’ qualification (defined as physicians who have completed 3 years of postgraduate training but are not yet eligible for a specialist title).

### Exclusion criteria

Physicians who were involved in the development of either e-learning programme, who have previously been exposed to I-CARE materials or have already completed the MI e-learning programme offered to the control group, or who do not understand French, will be excluded.

### Study procedure

The study flow diagram is presented in figure 1. PCPs will access the study website to review the participant information sheet and provide electronic consent, after which they will complete a self-administered online baseline questionnaire. Participants will then be randomised to either the I-CARE (intervention) or MI (control) e-learning programme. The allocated programme will be accessible for 6 weeks, with regular automated reminders. Access to both e-learning programmes will be provided free of charge.

**Figure 1 F1:**
[figure not shown]
Study flow diagram. I-CARE, Improving Care and Access for Rainbow Equity; MI, motivational interviewing; PCPs, primary care physicians.

Once participants have completed their allocated e-learning programme—or, at the latest, 6 weeks after completing the baseline questionnaire if they do not complete the training programme—they will be invited to complete a self-administered online postintervention questionnaire. A final self-administered online follow-up questionnaire will be completed at the 3-month follow-up assessment. Participants who complete all questionnaires and the allocated e-learning programme will receive six CME credits as well as CHF 50 (about USD 64) in compensation. All questionnaires will be hosted online using REDCap (REDCap Consortium, Vanderbilt University, Nashville, Tennessee).^18
19^

All three questionnaires will assess effectiveness outcomes. The baseline questionnaire will also collect sociodemographic characteristics, while the postintervention questionnaire will assess participants’ satisfaction with the training programme. All appropriate measures have been taken to minimise participant errors during questionnaire completion, including prior cognitive testing and pilot testing, explicit drop-down response options, built-in skip logic, mandatory fields for key variables, standardised response formats and range and plausibility checks for numerical entries.

Recruitment began with the pilot phase on 10 July 2026 and is planned to continue until 31 December 2027. Data collection is expected to be completed in 2028, and the study is expected to be completed by 31 March 2029, including publication and dissemination activities.

### Pilot phase

To assess the feasibility of the study procedures and instruments under field conditions, we will conduct an internal pilot study.^20^ Five hundred PCPs randomly selected from the target population of French-speaking PCPs in Switzerland will be invited to participate in the pilot. The number of invited PCPs was chosen to allow estimation of key study process parameters with sufficient precision to inform progression to the main trial. In line with the internal pilot design, data collected during the pilot will be retained and included in the final trial dataset, provided that pilot findings do not lead to substantial modifications of the protocol, study procedures or outcome measurement instruments. The pilot will use the same design and study procedures as the main trial, except that recruitment will rely exclusively on postal invitations to sampled PCPs. Any changes to the protocol, study procedures or outcome measurement instruments will be communicated to the Central Ethics Commission of the University of Lausanne and described in subsequent publications.

#### Intervention and comparator

I-CARE is a novel self-directed e-learning programme designed to improve PCPs’ knowledge, attitudes, skills and behaviours related to LGBTI people and their healthcare needs. Its development was led by RB and PB in collaboration with PCPs, field experts, academic institutions (the Faculties of Medicine and University Hospitals of Lausanne and Geneva, and nursing schools), public health authorities in the canton of Vaud and French-speaking LGBTI community organisations.^21^ The programme comprises 23 video capsules (5–15 min each), organised into four thematic modules spanning three competency domains: knowledge—(1) introduction to sexual and gender diversity (terminology and key concepts, mechanisms of stereotyping, discrimination and violence, and specific life-course experiences) and (2) social determinants of LGBTI health (fundamental causes of health inequities, intersectionality, health status and access to care); attitudes—(3) inclusive communication in primary care (affirmative attitudes and language, and a welcoming and inclusive practice environment); and skills—(4) specific healthcare needs in primary care settings (sexual health history-taking; mental and relational health; and the specific needs of trans and non-binary people, intersex people, cisgender non-heterosexual people, older LGBTI people and rainbow families). A detailed description of the programme’s development and contents is available elsewhere.^21^ It is informed by the Minority Stress Model^22^ and the Cultural Competence in Healthcare Delivery framework,^23^ with a particular focus on cross-cultural communication and health equity.^11^ Completion of the programme requires approximately 3–5 hours.

Participants in the control group will follow a different e-learning programme that does not include specific content on LGBTI health but is comparable to I-CARE in format and duration. The control programme, *Entretien motivationnel: Cours de base pour médecins de premier recours* (University of Geneva), introduces MI for PCPs. This active control was preferred over a no-intervention condition to equalise exposure to e-learning content, engagement and incentives across arms, to minimise the risk of differential attrition and to support partial blinding to the study hypothesis. While MI promotes patient-centred communication skills applicable to all patients, including LGBTI patients, the programme contains no LGBTI-specific content, thereby preserving the contrast between arms on the outcomes of interest.

### Blinding

Participants will be informed that they are taking part in a study evaluating the effectiveness of two e-learning programmes for the CME of PCPs. In accordance with the approved ethics protocol, they will not initially be informed that the primary objective is to assess the effectiveness of the I-CARE programme specifically, in order to minimise response bias. PCPs will, therefore, be partially blinded to the study hypothesis, while remaining fully informed about the nature of the training they receive. Questions related to both training programmes, including MI and LGBTI healthcare, will be presented in a balanced manner.

### Randomisation

Each participant who completes the baseline questionnaire will be randomised (1:1) to either the intervention group, receiving an invitation and access to the I-CARE e-learning programme, or the control group. The randomisation will be stratified by sex assigned at birth (male or female) and age category, as physicians’ attitudes towards sexual and gender minorities have been shown to vary by gender and by generation, with earlier year of graduation and male gender predicting more stigmatising responses.^24
25^ Stratification protects against chance imbalance between arms on these prognostic factors. Three age categories will be used: PCPs born after 1980 (Generation Z and Millennials); PCPs born between 1965 and 1980 (Generation X) and PCPs born before 1965 (Baby Boomers generation or older ones if any). Allocation tables will be generated using Stata V.19 (StataCorp LLC, College Station, Texas) with block randomisation (block size of four) to ensure balanced distribution between the intervention and control groups.^26^ Participant allocation will be implemented automatically in REDCap.

### Primary and secondary outcomes

Two primary outcomes will be evaluated: knowledge and attitudes regarding LGBTI patients and their healthcare needs at the postintervention assessment. Superiority will be declared if the intervention group is statistically significantly superior to the control group on at least one primary outcome and statistically significantly inferior on neither primary outcome. Secondary outcomes include knowledge and attitudes at the 3-month follow-up assessment as well as skills in caring for LGBTI patients, self-reported behaviours towards LGBTI patients and the use of LGBTI-friendly environmental cues in clinical practice at both postintervention and 3-month follow-up assessments.

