### Sample size calculations

Based on previous research,^33^ we expect an effect size of Cohen’s d=0.31 on the Knowledge subscale of the QUIRKS-Provider scale. Using generalised estimating equations (GEE),^34^ and assuming 80% power, a two-sided significance level of 0.05, an intraindividual correlation of 0.4, and 20% loss to follow-up, we estimated that 474 participants would be required to detect this effect at the postintervention assessment. Recruiting this number of participants appears feasible, even with a low participation rate. As the marginal cost of including additional participants is negligible, no upper limit on the sample size has been set.

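### Superiority can be won on either of two primary outcomes, yet the only stated level is an undivided two-sided 0.05 and no multiplicity adjustment is named

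*Protocol article*

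**What the plan says.** In the protocol article, the section Primary and secondary outcomes sets two primary endpoints: "Two primary outcomes will be evaluated: knowledge and attitudes regarding LGBTI patients and their healthcare needs at the postintervention assessment". The decision rule follows: "Superiority will be declared if the intervention group is statistically significantly superior to the control group on at least one primary outcome", with the further condition "and statistically significantly inferior on neither primary outcome". The Abstract (Methods and analysis) repeats the rule.

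The only significance level is in Sample size calculations: "assuming 80% power, a two-sided significance level of 0.05". It belongs to a calculation for one of the two outcomes: "we expect an effect size of Cohen’s d=0.31 on the Knowledge subscale of the QUIRKS-Provider scale". No effect size is given for attitudes.

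The section Statistical analyses covers the GEE model with equal baseline means, the ANCOVA fallback, sensitivity analyses, missing data and the complier analysis. Neither there nor elsewhere does the article mention splitting alpha, Bonferroni, Holm, a testing order or any other multiplicity procedure.

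**The concern.** Two primary outcomes need no adjustment when both must succeed. Here either one is enough for a single overall claim that I-CARE is superior. Under such a rule each outcome gives the trial a separate chance of a false win, so the trial-level error exceeds that of one test unless alpha is controlled.

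The condition about inferiority may look like a safeguard against this. It blocks a claim only when the two outcomes are significant in opposite directions, which is rare when the programme has no effect. At stake is the trial's headline conclusion, which could rest on one of two uncorrected tests.

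**Working it through.** **Inputs.** From Sample size calculations: d = 0.31 on knowledge, two-sided alpha 0.05, power 80%, within-person correlation 0.4, loss 20%, total 474. From Study design and setting: 1:1 allocation. The correlation between the two outcomes is not given; I assume 0 to 0.9.

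**1. Which alpha does 474 use?** With change-score variance, the number per arm is

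n = 2 × ((1.960 + 0.842)/0.31)² × 2(1 − 0.4) = 163.35 × 1.2 = 196.02, rounded up to 197.

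Inflating for loss: 197 × 1.2 = 236.4, rounded up to 237 per arm, so 2 × 237 = 474. This is the protocol's figure exactly, at an undivided 0.05. Other routes at 0.05 do not give it: change score with division by 0.8 gives 494, post-only variance gives 394 or 410, and constrained-baseline variance (factor 1 − 0.4²) gives 332 or 346. The matching route at 0.025 gives 237.38, so 238 per arm; 238 × 1.2 = 285.6, so 286 per arm and 572 in total.

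**2. False-superiority rate of the rule.** Let Z1 and Z2 be the two test statistics, bivariate normal with correlation r and no true effect on either outcome. The full rule has probability

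P(Z1 > 1.96 or Z2 > 1.96) − 2 × P(Z1 > 1.96 and Z2 < −1.96).

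At r = 0 the first term is 1 − 0.975² = 4.94%, and the second is 2 × 0.025 × 0.025 = 0.125%. The result is 4.81%.

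| Correlation (assumed) | At least one superior | Full rule | Ratio to 2.5% |
|---|---|---|---|
| 0 | 4.94% | 4.81% | 1.93 |
| 0.4 | 4.66% | 4.66% | 1.86 |
| 0.7 | 4.17% | 4.17% | 1.67 |
| 0.8 | 3.90% | 3.90% | 1.56 |
| 0.9 | 3.52% | 3.52% | 1.41 |

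The inferiority condition removes 0.125 percentage points at r = 0 and less than 0.005 at r = 0.4.

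**3. Rate after adjustment.** With no true effect, the first Holm step tests the smaller p-value at two-sided 0.025. The chance of at least one superior result is then 1 − 0.9875² = 2.48% at r = 0, 2.32% at 0.5 and 2.01% at 0.8. The inferiority condition can only lower these.

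**4. Power for knowledge at 474.** With 20% loss, 474 × 0.8 leaves about 379 analysed. Power = Φ(0.31/√(4f/379) − z), where z is 1.960 at two-sided 0.05 and 2.241 at two-sided 0.025.

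| Variance basis | f | 0.31/SE | Power at 0.05 | Power at 0.025 |
|---|---|---|---|---|
| Constrained baseline, 1 − 0.4² | 0.84 | 3.29 | 90.9% | 85.3% |
| Change score, 2(1 − 0.4) | 1.20 | 2.75 | 78.7% | 69.6% |

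The first row matches the model in Statistical analyses if the working correlation is exchangeable at 0.4, which is an assumption. The second row is the basis that reproduces 474.

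**The case against.** **The per-test level is an inference.** The article nowhere says that knowledge and attitudes are each tested at 0.05. The level appears only as a sample-size input for knowledge, and an analysis plan that is not shown may hold a multiplicity procedure. This stands as a limit on certainty, and the error rates are conditional on that level. It does not remove the point. The article itself fixes the either-outcome rule, and its sample size reproduces exactly at the full 0.05. An adjustment placed elsewhere would leave the stated alpha and power wrong for the first confirmatory step. A post-only calculation at 0.025 with the loss multiplier gives 476, close to 474, but it ignores the stated correlation and contradicts the stated alpha, so it is not evidence of a hidden split.

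**The rate stays below 5%.** This is true of false superiority. But a two-sided 0.05 test allows 2.5% in the favourable direction, and that is the right comparison for a claim of superiority.

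**Stronger readings to avoid.** A reader might infer that the false-superiority rate is 9.75%. That is the chance of any significant result on either of two independent outcomes, and it includes results favouring the control, which cannot produce a superiority claim under this rule. A reader might also say without qualification that the error nearly doubles. That holds at low to moderate correlation; at 0.9 the factor is 1.4, and the documents do not give the correlation.

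**Adjustment is not free on every basis.** This stands. On the variance that reproduces 474, power at the first step is about 70%, below the planned 80%.

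**Conclusion.** The point holds. As written, the rule lets one overall claim be won on either of two outcomes with no named adjustment, and the only stated level is undivided. If each outcome is tested at two-sided 0.05, false superiority under no effect on either is about 3.5% to 4.8%, which is 1.4 to 1.9 times the 2.5% of one test. This rests on approximately normal test statistics and an assumed correlation from 0.9 down to 0. Inflation is present throughout that range, and the inferiority condition does not control it.

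Because the defect lies in the decision rule that the article itself fixes, it is more than detail left to an analysis plan.

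**What to change.** In the Abstract and in Primary and secondary outcomes, state that superiority on at least one primary outcome is judged after Holm adjustment: the smaller p-value at two-sided 0.025 and, if that is significant, the other at 0.05. Keep the condition that neither outcome may be significantly worse, and state that it is tested at unadjusted two-sided 0.05. Adjusting that condition would weaken the safeguard, and dropping it would lose it.

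In Sample size calculations, restate the power for knowledge at the 0.025 step and name the variance basis. With 474 randomised and 20% loss it is about 85% under the constrained-baseline model that the protocol plans (exchangeable correlation 0.4 assumed) and about 70% under change-score variance.

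The cost is a few sentences in the protocol, carried into the analysis plan and registry entry, and a less favourable power figure for the first step. No extra participants are needed if power is restated on the planned constrained-baseline analysis. If the change-score basis is kept, the same route gives 572 rather than 474; the protocol sets no upper limit on recruitment. Recruitment is planned to run to 31 December 2027, so the change can be prespecified before the outcomes are analysed.
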